##### Second Phase

Participants experiencing adequate relief symptoms during phase 1 will proceed to phase 2. During this phase (reintroduction), which will last for 6 to 8 weeks, participants will determine their tolerance to individual FODMAP subgroups such as fructose, lactose, galacto-oligosaccharides, fructans, and polyols. In this phase, we will find out which FODMAPs can be tolerated by introducing only one FODMAP subgroup at a time, typically for three days, with three washout days in between subgroups introductions [18]. At this stage, participants will be encouraged to use a diary to identify trigger foods and to record symptom responses to set filters in the Monash FODMAP app during the third phase. Details regarding the Monash FODMAP app are provided in Appendix A.

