### 2.5. Consultations

After the initial consultation, participants will meet the same dietician on subsequent visits, physically or virtually. These visits are scheduled to occur up to four weeks after intervention initiation for the NICE group and six months after the first visit. In the MED-LFD group, visits are scheduled at the end of the restrictive phase to assist participants with implementing reintroduction, at the end of the reintroduction phase, and six months after the first visit.

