#### 2.8.2. Adequate Relief

Adequate relief (AR) is one of the most commonly used endpoint measures in IBS randomized controlled trials [35,36]. It will be evaluated with a single-item question, asking the participant: “In the last seven days, have you experienced adequate relief of your IBS symptoms?”. AR will be assessed through weekly telephone contact over four weeks for the NICE group and during the elimination reintroduction phases for the MED-LFD group. AR is achieved if positive answers are received in more than 50% of recordings within the given period. According to the study design, AR will be measured once after six months in both groups to evaluate symptom relief during the last week of follow-up.

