### 2.9. Study Timepoints

Three study timepoints are anticipated: Baseline: Two to four days before intervention initiation; first follow-up: at 4 weeks following the introduction of the dietary plan for the NICE group and at the end of the reintroduction phase for the MED-LFD group, anticipated to last on average 6–8 weeks (2–4 days’ time window); second follow-up: at six months (1-week time window), as shown in Figure 1, which also illustrates the procedures to be performed at each timepoint.

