### 2.10. Study Endpoints

The study’s primary endpoint is the change from baseline of IBS-SSS at the first and the second follow-up. The co-primary endpoint is the rate of responders for each dietary intervention, defined by a ≥50-point reduction in IBS-SSS, which has been shown to be a clinically significant improvement [21,37], at the first and second follow-ups. Secondary endpoints measured at both follow-ups will include the rate of subjects reporting AR and changes in IBS-QoL, SF-12, HADS, and GSRS-IBS. Adherence to dietary intervention, use of rescue medications, rate of participants who achieve IBS-SSS < 175, discontinuation rate (and causes), and AE/SAEs comprise also secondary endpoints.

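### MED-LFD participants without adequate relief in phase 1 have no defined first follow-up, so the primary comparison at that timepoint would set a response-selected MED-LFD group against unselected NICE participants

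*Protocol article*

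**What the plan says.** Four parts of the protocol article bear on this point.

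- **Entry to reintroduction** (Section 2.4.3, Second Phase), MED-LFD arm only: "Participants experiencing adequate relief symptoms during phase 1 will proceed to phase 2". The only definition of adequate relief is in Section 2.8.2: "AR is achieved if positive answers are received in more than 50% of recordings within the given period". No route is described for those who do not reach it.
- **First follow-up** (Section 2.9). For the control arm: "first follow-up: at 4 weeks following the introduction of the dietary plan for the NICE group". For the intervention arm: "at the end of the reintroduction phase for the MED-LFD group, anticipated to last on average 6–8 weeks". The control assessment carries no response condition.
- **Endpoints** (Section 2.10). The "primary endpoint is the change from baseline of IBS-SSS at the first and the second follow-up". Also: "The co-primary endpoint is the rate of responders for each dietary intervention, defined by a ≥50-point reduction in IBS-SSS", read at the same two follow-ups. Adequate relief and the changes in IBS-QoL, SF-12, HADS and GSRS-IBS are secondary endpoints at both follow-ups.
- **Analysis populations** (Section 2.11.2). Changes in IBS-SSS and the other scores are assigned to the per-protocol (PP) population alone. The responder, adequate-relief and IBS-SSS <175 rates are assigned to both ITT and PP.

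Section 2.5 adds that in the MED-LFD arm "visits are scheduled at the end of the restrictive phase to assist participants with implementing reintroduction, at the end of the reintroduction phase" and at six months. The visit at the end of restriction is a dietician consultation and is not one of the three study timepoints in Section 2.9.

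**The concern.** One arm's assessment is tied to completing a phase that is open only to participants who have already improved. A participant who never starts reintroduction never ends it, so the schedule as written gives that person no date for the first-follow-up IBS-SSS. The other arm has no such filter.

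Adequate relief and IBS-SSS change both measure improvement in IBS symptoms, so a positive correlation between them is to be expected. Selecting on the first raises the mean of the second. Randomisation does not protect a comparison in which one arm is filtered on response after allocation. With IBS-SSS change analysed in the PP population only, no planned ITT analysis of the primary endpoint would show or offset the selection. A later analysis plan can say how missing values are treated, but it cannot recover questionnaires that were never scheduled.

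**Working it through.** **Step 1: the text side by side.**

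| | MED-LFD | NICE |
|---|---|---|
| Condition before first follow-up | adequate relief in phase 1, then reintroduction | none |
| First follow-up | end of reintroduction | 4 weeks |
| First follow-up if the condition is not met | not stated | not applicable |
| Second follow-up | six months | six months |

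The weekly calls in phase 1 (Section 2.8.2) collect the relief answer, not IBS-SSS, so they cannot stand in for the missing assessment.

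**Step 2: inputs for the size.**

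- From Section 2.11.1: improvements of 100 and 59 points, so a planned difference of 100 − 59 = 41; SD 60; 54 per group; a 10% allowance, giving 54 × 0.9 = 48.6, about 49 evaluable NICE participants.
- Assumed, because the documents do not give them: the share p of the MED-LFD arm that proceeds, 0.6 to 0.8; and the correlation r between the latent phase-1 relief that decides progression and IBS-SSS change at first follow-up, 0.3 to 0.7.

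The stated 54 per group does not itself follow from the stated inputs: 2 × (60/41)² × (1.960 + 0.842)² = 33.6, so 34 per group, and 34/0.9 = 37.8, so 38. That is a separate matter. The bias below depends only on SD, p and r.

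**Step 3: spurious gain with no true difference.** Under a bivariate normal model in which only the top share p on phase-1 relief is observed,

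gain = r × SD × φ(c)/p, with c = Φ⁻¹(1 − p).

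- p = 0.6: c = −0.253, φ(c) = 0.386, φ(c)/p = 0.644.
- p = 0.8: c = −0.842, φ(c) = 0.280, φ(c)/p = 0.350.

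| p | r = 0.3 | r = 0.5 | r = 0.7 |
|---|---|---|---|
| 0.6 | 60 × 0.3 × 0.644 = 11.6 | 19.3 | 27.0 |
| 0.8 | 60 × 0.3 × 0.350 = 6.3 | 10.5 | 14.7 |

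As a share of the planned 41 points: 6.3/41 = 15% up to 27.0/41 = 66%.

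**Step 4: effect on the test.** Take 49 NICE participants against 49p observed MED-LFD participants (29 or 39), SD 60 in both arms, two-sided 5%. At p = 0.6 the standard error is 60 × √(1/29 + 1/49) = 14.06, and the false-positive rate runs from 13% (r = 0.3) to 49% (r = 0.7). At p = 0.8 the standard error is 12.88 and the rate runs from 8% to 21%. Allowing for the smaller spread in a selected group raises the upper values to about 56% and 23%.

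**Step 5: responder rate (≥50-point reduction).** With a true mean change of 59 in both arms, the rate in the whole arm is Φ((59 − 50)/60) = Φ(0.15) = 56%. Over the same ranges of p and r, the rate among progressors is 60–76%, which favours MED-LFD. If an ITT analysis counts non-progressors as non-responders, the MED-LFD rate is 38–53%, which counts against MED-LFD. The sign depends on a counting rule that the article does not state.

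**The case against.** The strongest reply is that non-assessment is inferred. No section says that participants without phase-1 relief are withdrawn or left unmeasured. Section 2.5 lists the later visits for the MED-LFD group without a response condition, ITT is defined as all randomised participants, and a condensed article may leave the handling of non-progressors to the full protocol. This stands in part. A reader might infer that the MED-LFD first-follow-up data will come from early relievers only, and the text does not go that far. But more than a detail is missing: the timepoint that is stated cannot be applied to someone who does not enter reintroduction. The 6–8 weeks given with it is an expected phase duration, not a calendar date for everyone.

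Other stronger readings also fail:

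- **The PP rule by itself removes non-relievers.** PP means strict adherence to the protocol, and someone who does not proceed under the protocol's own rule has adhered. Such a person would drop out of the comparison through a missing value, not through the definition.
- **Every endpoint is biased towards MED-LFD.** Step 5 shows that the ITT rates could be biased either way. Progressors are also assessed after weeks of FODMAP reintroduction. If that provokes symptoms it pulls against MED-LFD, and the model leaves it out.
- **Both primary timepoints are affected.** The six-month visit is fixed by calendar in both arms.
- **The trial would be left underpowered.** On the protocol's difference of 41 and SD of 60, with 54 NICE participants, power is still 92% if 80% of the MED-LFD arm is observed and 86% if 60% is. The problem is bias, not sample size.

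**Conclusion.** The point holds for the first follow-up. As written, MED-LFD participants who do not proceed to reintroduction have no defined assessment there. The observed PP comparison of IBS-SSS change would then set participants selected for early relief against unselected NICE participants, and this selection favours MED-LFD.

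The mechanism, and the direction of the selection effect for the PP continuous endpoints, follow from the protocol's text together with a positive correlation between relief and IBS-SSS change. The size does not: 6–27 points rests on assumed progression shares of 60–80% and correlations of 0.3–0.7, and on a normal selection model. For the responder, adequate-relief and IBS-SSS <175 rates under ITT, the direction is undetermined. The six-month comparison is not gated by definition. The point matters because it touches one of the two timepoints of the primary and co-primary endpoints and cannot be repaired once the assessments have been missed.

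**What to change.** Reconcile the Second Phase text of Section 2.4.3 with Sections 2.9 and 2.11.2:

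1. Set the first follow-up at a stated number of weeks since intervention start for every randomised participant, whether or not they enter phase 2.
2. State that MED-LFD participants who do not proceed complete IBS-SSS and the other questionnaires at that time and again at six months.
3. Analyse IBS-SSS change in the ITT population, with PP as supportive. Without items 1 and 2, an ITT analysis would have no first-follow-up values for the non-progressors.

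The rule on who proceeds to reintroduction stays as it is; only who is measured, when, and in which population changes. The six-month visit date needs no redefinition.

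The cost is a few more questionnaires from people already enrolled. The first follow-up may no longer coincide exactly with the end of reintroduction, which shifts what it estimates and, in the stool-sample subgroup, when samples are taken. The MED-LFD estimate may also become less favourable.

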##### Third Phase

After completing the reintroduction phase, participants are expected to be able to identify the FODMAPs that trigger their symptoms and those that they can tolerate (personalization phase). Thereafter, they will follow a long-term diet that encourages nutritional adequacy, while they can customize the Monash FODMAP app’s food guide by setting filters that match their personal FODMAP sensitivities [14]. The personalized diet will include well-tolerated foods and FODMAPs, while poorly tolerated FODMAPs will be restricted to a level that provides adequate symptom control.

### 2.5. Consultations

After the initial consultation, participants will meet the same dietician on subsequent visits, physically or virtually. These visits are scheduled to occur up to four weeks after intervention initiation for the NICE group and six months after the first visit. In the MED-LFD group, visits are scheduled at the end of the restrictive phase to assist participants with implementing reintroduction, at the end of the reintroduction phase, and six months after the first visit.

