### 2.7. Adverse Events, Serious Adverse Events, and Study Discontinuation

An adverse event (AE) is any undesirable or unfavorable medical occurrence in a participant or subject who is exposed to a medicine, a medical product, or an intervention like diet. An AE does not necessarily have a causal relationship with the medicine, product, or intervention. An AE can be any sign, symptom, or disease that is temporally associated with the use of the medicine, product, or intervention, whether or not considered related to it. An AE is serious and should be reported when the participant’s outcome is death, life-threatening, hospitalization, disability, or other significant impairment. All AEs will be recorded and causality association with treatment will be assessed. All serious adverse events (SAEs) will be reported according to the local legislation.

Participants can terminate their study participation at any time if they wish, or due to the occurrence of AE, progression, or intractable symptoms they are unable to control with the interventions and/or rescue medications. All discontinuations and their reason will be recorded.

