#### 2.8.3. Adherence

Adherence to the diets will be assessed weekly by telephone, by asking the question: “How often did you follow your weekly diet?” and scored on a 5-point Likert scale (never, rarely, sometimes, most of the time, and every day).

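### Stated contact and planned food challenges differ by arm, so the AE and rescue-medication comparison could reflect unequal opportunity to report and expected challenge symptoms as well as harm

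*Protocol article*

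**What the plan says.** **Endpoints.** Section 2.10 lists "use of rescue medications, rate of participants who achieve IBS-SSS < 175, discontinuation rate (and causes), and AE/SAEs comprise also secondary endpoints". Section 2.11.2 assigns AEs to the ITT population and rescue use to the per-protocol population. Section 2.11.3 compares categorical variables between arms with a chi-squared test and states no adjustment for exposure or contact.

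**Contact.** For NICE, section 2.5 has visits "scheduled to occur up to four weeks after intervention initiation for the NICE group and six months after the first visit". For MED-LFD it has visits at the end of restriction, then "at the end of the reintroduction phase, and six months after the first visit". Section 2.8.2 sets the adequate-relief calls as "weekly telephone contact over four weeks for the NICE group and during the elimination reintroduction phases for the MED-LFD group". Section 2.8.3 adds that "Adherence to the diets will be assessed weekly by telephone", with no end date and no difference between arms. Section 2.9 puts the first follow-up at week 4 in NICE and at the end of reintroduction in MED-LFD; the second is at six months in both.

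**Challenges.** Under Second Phase, MED-LFD participants with adequate relief in phase 1 test their tolerance by "introducing only one FODMAP subgroup at a time, typically for three days, with three washout days in between subgroups introductions". Five subgroups are named, and a symptom diary is encouraged. NICE has no counterpart.

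**Definition and recording.** Section 2.7 says "An AE can be any sign, symptom, or disease that is temporally associated with the use of the medicine, product, or intervention", whether or not it is thought related, and makes no exception for challenge symptoms. Sections 2.6 and 2.7 say that all rescue medication and all AEs will be recorded, without saying at which contacts. Section 2.6 allows rescue medication when symptoms worsen.

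**The concern.** A comparison of AE or rescue rates is like for like only if both arms have the same chance to report over the same period, and if the same kinds of event are counted. Three features of the plan work against this:

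1. Weekly telephone contact with a stated duration lasts longer in MED-LFD, so events may be reported there that NICE participants would have to recall at month six.
2. Any count up to the first follow-up covers a longer period in MED-LFD.
3. MED-LFD includes planned exposures meant to show which FODMAPs are not tolerated. The resulting symptoms can qualify as AEs and prompt rescue use, and nothing separates them from unexpected events.

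Each feature tends to raise the recorded MED-LFD rate. The trial's safety statement could then be unfavourable to MED-LFD, or uninterpretable, for reasons unrelated to unintended harm.

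**Working it through.** The plan gives no figure for event rates or capture, so there is none to reproduce. The calculations below show the possible size.

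**Inputs from the article.** NICE adequate-relief calls: 4 weeks. Reintroduction: 6 to 8 weeks. Follow-up: six months, taken as 26 weeks. Group size: 54.

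**Assumptions.** The length of the restrictive phase is not stated. If the 6 to 8 weeks in section 2.9 is the whole MED-LFD period, called weeks are 6 to 8. If it follows an assumed 4-week restriction, they are 10 to 12. The range used is therefore 6 to 12. True event rates are constant and equal in both arms. Capture is 90% in called weeks and *c* in uncalled weeks, with *c* = 70%, 40% or 20%.

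**Step 1: contact over six months.** Captured week-equivalents = 0.9 × called weeks + *c* × (26 − called weeks).

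| *c* | NICE, 4 called weeks | MED-LFD, 6 called weeks | MED-LFD, 12 called weeks | Ratio |
|---|---|---|---|---|
| 70% | 3.6 + 15.4 = 19.0 | 5.4 + 14.0 = 19.4 | 10.8 + 9.8 = 20.6 | 1.02–1.08 |
| 40% | 3.6 + 8.8 = 12.4 | 5.4 + 8.0 = 13.4 | 10.8 + 5.6 = 16.4 | 1.08–1.32 |
| 20% | 3.6 + 4.4 = 8.0 | 5.4 + 4.0 = 9.4 | 10.8 + 2.8 = 13.6 | 1.18–1.70 |

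If weekly calls run to month six in both arms and collect AEs, both arms have 26 called weeks and the ratio is 1.00.

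Not everyone enters reintroduction. If half do, and the rest have 4 called weeks, the 12-week case at *c* = 40% becomes (16.4 + 12.4)/2 = 14.4, a ratio of 14.4/12.4 = 1.16.

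**Step 2: unequal window at the first follow-up.** Suppose capture is complete but events are counted up to each arm's own first follow-up. The proportion with at least one event is 1 − (1 − p)^w, where p is the weekly probability and w the weeks elapsed.

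- p = 2%: NICE (w = 4) 7.8%; MED-LFD (w = 6 to 12) 11.4% to 21.5%.
- p = 5%: NICE 18.5%; MED-LFD 26.5% to 46.0%.

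With 54 per arm, a chi-squared test at 0.05 would reject 10% to 53% of the time in the first case and 17% to 88% in the second, although the weekly rates are equal. With a common 12-week window it rejects 5.1% and 4.4% of the time.

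**Step 3: challenges alone.** Give both arms equal and complete capture for 26 weeks, with p = 2%. Let each of five challenges produce a recorded symptom with assumed probability q.

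- NICE: 1 − 0.98^26 = 40.9%.
- MED-LFD: 1 − 0.98^26 × (1 − q)^5 = 54.2% at q = 5% and 65.1% at q = 10%.

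The chi-squared test rejects 27% and 70% of the time. These figures assume that every MED-LFD participant takes all five challenges. If half do, the MED-LFD proportions fall to (40.9 + 54.2)/2 = 47.6% and (40.9 + 65.1)/2 = 53.0%. Equalising contact does not remove this component.

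**The case against.** The strongest reply is that the article never says AEs or rescue use are elicited at the adequate-relief calls. The visits in section 2.5 are dietician consultations, the calls in 2.8.2 ask one relief question, and how AEs are elicited may be set out in a fuller protocol or case report form. The adherence calls in 2.8.3 are weekly with no stated end and no arm difference; read literally, they give both arms the same contact throughout. This stands. It means the contact effect is possible rather than shown, and that 1.00 belongs in the range.

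A reader might infer more than the article supports:

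- **That two equally safe diets would necessarily show different rates.** This needs AEs to be collected at the unequal calls, which is not stated. Challenge symptoms are also real consequences of the MED-LFD strategy, not recording artefacts. The difficulty is that they are merged with other events.
- **That every positive challenge becomes an AE, up to five per MED-LFD participant.** The definition says what an AE can be and causality is to be assessed. Five is an upper bound, and only for those who enter reintroduction.
- **That NICE has no contact between week 4 and month six.** This holds only if the adherence calls stop early. If all weekly calls stop with the relief calls, MED-LFD also has 14 to 20 uncalled weeks.
- **That discontinuation is biased in the same way.** It is counted in the ITT population, and a withdrawal during the same six months does not depend on call frequency to be noticed. Challenges might raise it and closer contact might lower it, so no direction is shown.

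The reply does not remove the different first follow-up times, the challenges in one arm only, or an AE definition that does not set their symptoms apart. The article fixes all three. A promise to record all AEs does not equalise the chance to report them.

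**Conclusion.** The point holds for AEs and rescue use, as a possible bias rather than a demonstrated one. On the stated schedule the two rates are not assured to be like for like, for three reasons: possibly unequal opportunity to report, unequal windows if events are counted to the first follow-up, and the merging of expected challenge symptoms with other events.

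The contact ratio is 1.00 if weekly adherence calls continue to month six in both arms and collect AEs, and otherwise about 1.02 to 1.70. That range rests on assumed capture rates and on reading the MED-LFD call period as 6 to 12 weeks. The challenge component is separate and does not depend on call frequency; its size depends on the assumed symptom probability and on the share entering reintroduction. No claim is made about six-month discontinuation. The change is worth making because these are named endpoints and events not asked about at the time cannot be recovered reliably at analysis.

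**What to change.** 1. Ask one standard AE and rescue-medication question at identical calendar times in both arms up to month six. Use the section 2.8.3 adherence calls if they continue to month six, and state that they do. Otherwise use short calls at the same weeks in both arms.
2. Compare AEs and rescue use over common calendar windows, for example weeks 0 to 4 and week 4 to month six, rather than up to each arm's own first follow-up.
3. Pre-define a separate category for symptoms confined to a planned challenge and its washout. Show AE and rescue totals with and without it.

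The cost is case report form wording, extra table splits and, if the adherence calls stop early, a few short contacts, mainly in NICE. The downside is slightly more contact in NICE than now planned. No diet or rescue rule changes.
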